### Large for gestational age (LGA) infants

The differences in the proportions of babies that are LGA will be compared. LGA infants will be defined in keeping with other trials [38] as a birth weight ≥90^th^ centile for gender and gestation, as well as a birth weight > 4000 grams. These data will be obtained from a review of medical records and will be reported using both criteria.

### Psychological health

Validated scales, where available, will be used to measure self- reported psychological wellbeing and engagement in behaviour change: anxiety; depression; self- efficacy and readiness to change behaviour will be measured at enrolment and at 36 weeks gestation using questionnaires in hard copy.

### Anxiety

Anxiety will be measured using the short version of the Speilberger State-Trait anxiety inventory (STAI-State) [47]. Respondents use a four point scale for six items to indicate how they feel now (1 = Not at all to 4 = Very much). With reversing of specific responses, mean scores are reported and higher scores indicate greater anxiety.

### Depression

Depression will be measured using the Beck Depression Inventory II [48] a 21 item scale with respondents selecting from one of four statements. Each response is assigned a score of 0 to 3 and the total score is the sum of all responses. This scale has been validated to use in pregnancy; a cut off >16 affords a sensitivity of 0.83, a specificity of 0.89, positive predicted value of 0.50 and negative predictive value of 0.98 PPV [49]. The mean differences between groups will be compared.

### Self-efficacy

Self-efficacy related to healthy lifestyle changes in diet and exercise will be measured and the mean differences between groups will be compared. Self-efficacy related to eating will be measured using a 20 item, 10 point scale ranging from 0 (not confident) to 9 (very confident) [50]. Sub-scales of the Weight Efficacy Life-Style Questionnaire include: negative emotions, availability, social pressure physical discomfort and positive activities; the total score is the sum of all items. The Cronbach alpha coefficients of internal consistency ranged from 0.70 for positive activities to 0.90 for social pressure [50].

The Self-Efficacy for Exercise Scale will also be used and consists of nine items that respondents score from 0 (not confident) to 10 (very confident) [51]. The Cronbach alpha coefficient of internal consistency is 0.92 and reliability using the squared multiple correlation coefficient ranged from 0.38 to 0.76 [51].

### Readiness to change

Readiness to change, the importance of change and confidence in changing will be measured using the Readiness to Change Questionnaire [52] which researchers have modified for the weight loss context. This scale measures stages of change (pre-contemplation, contemplation and active) using 12 items each with a five point rating scale from 1 (strongly agree) to 5 (strongly disagree). Information from this scale will be used descriptively.

### Differences in plasma glucose levels

Differences in mean values of fasting, 1 hour and 2 hour plasma glucose levels from the OGTT will be compared using both ADIPS and IADPSG criteria in both groups.

### Economic evaluation

Resource use data will be collected from medical records and projections of health cost savings will be informed by pregnancy and birth outcome data.

### Power, sample size and retention

The primary outcome is the proportion of overweight and obese women diagnosed with GDM. The proportion of obese women diagnosed with GDM is 17% in a Victorian context [40]; a difference 10% effect size is considered clinically significant. It is estimated that 370 women are required (185 per study arm) in order to detect a difference of 10% between groups with 80% power at a 0.05 level of significance. With an approximate expected participation of 77% [53] and attrition rate of 15% [53] the required sample of 370 women will be recruited.

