### Aims

The primary aim of this trial is to measure the impact of the EDGE intervention compared to usual care on the incidence of GDM in overweight and obese women. The primary hypothesis is that women randomised to the EDGE intervention will have 10% fewer diagnoses of GDM than women in the control group. There are four secondary aims: to measure the impact of the EDGE intervention compared to usual care on 1) restricting gestational weight gain to the weight ranges recommended by the Institute of Medicine [29]; 2) reducing the incidence of babies born large for gestational age (LGA); 3) differences in blood glucose levels taken at the Oral Glucose Tolerance Test (OGTT) and 4) promoting self-efficacy and selected factors for psychological well-being.

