### Analyses

Initial analysis will examine baseline characteristics of all women, as an indication that the treatment groups were comparable for selected variables including, age, parity and BMI category. Primary and secondary outcomes will be analysed on an "intention to treat" basis. Differences between trial arms will use the Chi-squared statistic for categorical outcomes and Student’s t-test for continuous outcomes and 95% confidence intervals will be reported. Appropriate regression models will be employed controlling for co-variants. The fidelity of the intervention will be assessed and reported and the feasibility of the intervention will be considered in the process evaluation that will include the experience of participants and GP/PNs.

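### The 370 women needed for 80% power is also the recruitment target, so the 15% attrition the plan expects is not covered and the stated power does not hold

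*Protocol article*

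**What the plan says.** Everything needed is in the protocol article, mostly under Power, sample size and retention.

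- Control rate: "The proportion of obese women diagnosed with GDM is 17% in a Victorian context [40" (the citation bracket is cut off in the quote).
- Target effect: "a difference 10% effect size is considered clinically significant". The direction comes from Aims: "women randomised to the EDGE intervention will have 10% fewer diagnoses of GDM than women in the control group".
- Required number: "It is estimated that 370 women are required (185 per study arm"), set "with 80% power at a 0.05 level of significance".
- Expected losses: "With an approximate expected participation of 77% [53"], followed in the same sentence by "attrition rate of 15% [53] the required sample of 370 women will be recruited".
- Planned test, under Analyses: "Differences between trial arms will use the Chi-squared statistic for categorical outcomes". Continuity correction is not mentioned.

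No recruitment figure above 370 appears anywhere in the article.

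**The concern.** A power calculation gives the number of women who must have an outcome. If some are expected to be lost, the number recruited has to be larger, or the power has to be quoted for the smaller number left. Here the required number and the recruited number are the same, and the attrition rate stands between them without being used. The participation rate does not help: it determines how many women must be approached, not how many of those enrolled are analysed.

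At stake is the accuracy of the headline power claim for the primary outcome. The question is whether 370 already contains an allowance for loss and, if not, how much power is lost.

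**Working it through.** **Inputs.** From the article: control rate 0.17, intervention rate 0.07, alpha 0.05, power 80%, equal arms, attrition 15%, participation 77%. Two readings are assumed:

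- The 10% is an absolute difference. A 10% relative reduction (17% to 15.3%) would need about 14,700 women.
- The test is two-sided, which the article does not state. One-sided calculations give 260 women, or 298 with continuity correction, and so do not reproduce 370.

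**Step 1: reproduce 370.** With mean rate 0.12 and d = 0.10, the pooled formula is

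n' = [1.96·√(2·0.12·0.88) + 0.8416·√(0.17·0.83 + 0.07·0.93)]² / 0.10² = (0.9007 + 0.3822)² / 0.01 = 164.6 per arm.

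The continuity correction gives

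n = (n'/4)·[1 + √(1 + 4/(n'·d))]² = 184.04, rounded up to 185 per arm, or 370 in total.

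This matches the plan exactly before any allowance for loss.

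**Step 2: could 370 be an inflated smaller number?**

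| Starting number | Inflation for 15% | Total |
|---|---|---|
| Uncorrected, 330 | divide by 0.85 | 388 (390 if each arm is rounded up) |
| Uncorrected, 330 | multiply by 1.15 | 380 |
| Arcsine, 318 | divide by 0.85 | 374 |

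None gives 370. The article also ties 370 to the power statement before it mentions attrition.

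**Step 3: women left after attrition.** 370 × 0.85 = 314.5, about 157 per arm.

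**Step 4: power at 157 per arm, 17% versus 7%.**

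- Uncorrected formula: z = (0.10·√157 − 0.9007)/0.4541 = 0.776, power 78.1%.
- Corrected formula: inverting the correction gives an effective n' = (157 − 1/0.10)²/157 = 137.6. Then z = (0.10·√137.6 − 0.9007)/0.4541 = 0.600, power 72.6%.
- Exact power comes from summing the two binomial distributions over all tables that the test rejects.

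| Test | 185 per arm, formula | 157 per arm, formula | 157 per arm, exact |
|---|---|---|---|
| Continuity-corrected | 80.2% | 72.6% | 73.5% |
| Uncorrected chi-squared | 84.4% | 78.1% | 79.5% |

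**Step 5: detectable difference at 80% power, 157 per arm, control rate 17%.**

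| Test | Normal formula | Exact |
|---|---|---|
| Uncorrected | 10.2 points | 10.05 points |
| Continuity-corrected | 10.7 points | 10.6 points |

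**Step 6: numbers if 370 must have outcomes.** 370/0.85 = 435.3, so 436 randomised (218 per arm). 436/0.77 = about 566 approached.

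**The case against.** **The shortfall nearly vanishes under the test as named.** Analyses specifies a chi-squared test and no continuity correction. A conservative sample-size formula does not oblige the trial to use a conservative test. Uncorrected, the gap is 0.5 points (exact) to 2 points (formula). This stands and limits the size of the point. It does not restore 80%, and the article does not rule the correction out.

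**Loss on the primary outcome may be below 15%.** Under Data collection, GDM comes from hospital records with general practice records as back-up, so an unreturned questionnaire need not remove an outcome. With 10% loss (370 × 0.90 = 333, 166 per arm), uncorrected power would be 80.3% (81.8% exact). By the corrected formula it would still be short: n' = (166 − 10)²/166 = 146.6, z = (0.10·√146.6 − 0.9007)/0.4541 = 0.683, power 75.3%. The argument is plausible, but the article applies 15% to this sample without distinguishing outcomes. If a smaller loss is expected for GDM, the plan should say so.

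**The sentence may be a feasibility statement**, meaning that recruitment will continue until the required 370 is secured. The wording is loose enough to allow this, but what it says will be recruited is 370. If 370 was meant as the evaluable number, the number to enrol is not given.

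**An article condenses the protocol.** That excuses omissions. Here the required number, the attrition rate and the recruited number are all printed and do not fit together.

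**A stronger reading is tempting.** A reader might infer that the trial is seriously underpowered and that a null result would be misread. The documents do not support this. The detectable difference moves from 10 points to between 10.05 and 10.7, which would hardly change how a null result is read, and Analyses promises 95% confidence intervals that will show the precision achieved.

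**Conclusion.** The point holds. On the plan's own figures, 370 contains no allowance for the 15% attrition, and recruiting 370 does not deliver the stated 80% power. The shortfall is about 7 points by the continuity-corrected method that yields 185 per arm, and 0.5 to 2 points if the chi-squared test is run uncorrected. The 73% figure should not be quoted alone, because it applies only if a correction the article never mentions is used at analysis.

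This rests on an absolute 10-point difference, a two-sided test, the 17% control rate taken as given, and 15% loss applying to the primary outcome. It is a should-fix: a stated figure is wrong, by an amount that is small to moderate depending on the test, and the design itself is not invalidated.

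**What to change.** State which number 370 is, and make the other figures agree with it.

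- **If 370 is the number randomised:** say so, and restate power for about 314 evaluable women as about 73% (continuity-corrected) or about 78% by formula, 79.5% exact (uncorrected). Give the matching detectable difference, 10.7 or 10.2 points by formula (10.6 or 10.05 exact), and label the method.
- **If 370 is the number with outcome data:** say so, and give about 436 to randomise and about 566 to approach.

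In either case, say whether the chi-squared test is continuity-corrected and that it is two-sided, if that is intended. If loss on the record-based GDM outcome is expected to be below 15%, give that rate and use it.

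The first option costs a sentence or two, a slightly less favourable power figure and no extra participants. The second means randomising 66 more women (436 − 370).

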### Data collection

A record review from the local hospitals will be conducted after birth to provide data for GDM and gestational weight gain outcomes. Socio-demographic data, pregnancy and birth data will be collected from the medical records and used descriptively to interpret findings. Data will also be obtained from medical records of General Practices if required.

Self-reported baseline and outcome data will be collected using a paper based questionnaire. The initial questionnaire will be provided at recruitment and the second questionnaire will be posted at 36 weeks; reply-paid envelopes will be provided for both questionnaires.

### Ethics

Ethics approval to conduct this study has been provided by the Human Research Ethics Committee (HREC) of Barwon Health 12/108 and the project has been endorsed by Deakin University HREC.

### Analyses

Initial analysis will examine baseline characteristics of all women, as an indication that the treatment groups were comparable for selected variables including, age, parity and BMI category. Primary and secondary outcomes will be analysed on an "intention to treat" basis. Differences between trial arms will use the Chi-squared statistic for categorical outcomes and Student’s t-test for continuous outcomes and 95% confidence intervals will be reported. Appropriate regression models will be employed controlling for co-variants. The fidelity of the intervention will be assessed and reported and the feasibility of the intervention will be considered in the process evaluation that will include the experience of participants and GP/PNs.

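### For the twice-measured anxiety, depression and self-efficacy scales, the main analysis should be ANCOVA on the enrolment score; the only named test is a t-test

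*Protocol article*

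**What the plan says.** All references are to the protocol article.

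- **Psychological health.** Anxiety, depression, self-efficacy and readiness to change "will be measured at enrolment and at 36 weeks gestation using questionnaires in hard copy". Each scale therefore has an enrolment score as well as an outcome score.
- **Depression.** "The mean differences between groups will be compared".
- **Self-efficacy.** Self-efficacy for diet and exercise "will be measured and the mean differences between groups will be compared". Two scales are used, one for eating and one for exercise.
- **Anxiety.** The section says only that "mean scores are reported and higher scores indicate greater anxiety".
- **Readiness to change.** This scale is for descriptive use only.
- **Analyses.** Categorical outcomes get a chi-squared test. For the rest the plan is Student's "t-test for continuous outcomes and 95% confidence intervals will be reported". The next sentence reads "Appropriate regression models will be employed controlling for co-variants". It lists no covariates or outcomes and does not rank the regression against the t-test.

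No section says whether the t-test is applied to the 36-week score or to the change since enrolment.

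**The concern.** The enrolment score of a scale is often the best single predictor of its later score. The trial collects that score on four scales to be compared between arms, yet the one test it names has no covariate, and the regression sentence does not commit to using the score.

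Two things are at stake.

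- **Precision.** The trial was sized on gestational diabetes (GDM) alone, so nothing in the design secures precision for the scales. A t-test on the 36-week score leaves in the variance that the enrolment score explains. A t-test on change uses the enrolment score with a fixed weight of one, which is too much unless r is close to one.
- **Which result counts.** An unadjusted and an adjusted estimate are both planned and neither is named as the main one. If they differ, the article gives no rule for which to report first.

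**Working it through.** **1. The plan's own figure.** The only sample-size figure is for GDM: 185 per arm, 370 in total. The inputs, from Power, sample size and retention, are a control rate ("The proportion of obese women diagnosed with GDM is 17% in a Victorian context"), a 10-point difference (17% against 7%), 80% power and a 0.05 level, taken as two-sided.

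- Uncorrected: n = [1.960·√(2·0.12·0.88) + 0.842·√(0.17·0.83 + 0.07·0.93)]² / 0.10² = 164.6, so 165 per arm.
- With continuity correction: (164.6/4)·[1 + √(1 + 4/(164.6·0.10))]² = 184.04, so 185 per arm.

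The figure reproduces exactly. It concerns GDM and says nothing about the scales, for which no SD, target difference or power is given.

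**2. Inputs for the scales.**

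- Two measurements per scale (Psychological health).
- 185 per arm and 15% attrition (Power, sample size and retention). Applying the attrition to 185 gives 185 × 0.85 ≈ 157 per arm.
- The correlation r between the enrolment and 36-week scores is **not in the article**. It is assumed here over 0.3 to 0.7.
- The SD is assumed equal at the two times (needed only for the change score).

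**3. Formulas.** Variance of the between-arm difference, relative to a t-test on the 36-week score:

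- t-test on the 36-week score: 1
- t-test on change: 2(1 − r)
- ANCOVA: 1 − r²

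ANCOVA saves r² against the first. Against the second it saves 1 − (1 − r²)/[2(1 − r)] = (1 − r)/2. Since 2(1 − r) − (1 − r²) = (1 − r)² ≥ 0, ANCOVA is at least as precise as either t-test at every r.

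**4. Variance.**

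| Assumed r | 36-week t-test | Change t-test | ANCOVA | Saving against 36-week | Saving against change |
|---|---|---|---|---|---|
| 0.3 | 1.00 | 1.40 | 0.91 | 9% | 35% |
| 0.5 | 1.00 | 1.00 | 0.75 | 25% | 25% |
| 0.7 | 1.00 | 0.60 | 0.51 | 49% | 15% |

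Against the 36-week t-test, the confidence interval width is multiplied by √(1 − r²): 0.95, 0.87 and 0.71.

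**5. In trial terms, with 157 per arm.** The detectable difference at 80% power, in SD units, is (1.960 + 0.842)·√(2v/157), where v is the relative variance above. Power is for a difference of 0.3 SD, chosen only as an illustration.

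| Assumed r | Detectable: 36-week / change / ANCOVA | Power at 0.3 SD: 36-week / change / ANCOVA |
|---|---|---|
| 0.3 | 0.316 / 0.374 / 0.302 | 75.7% / 61.3% / 79.6% |
| 0.5 | 0.316 / 0.316 / 0.274 | 75.7% / 75.7% / 86.6% |
| 0.7 | 0.316 / 0.245 / 0.226 | 75.7% / 92.9% / 96.1% |

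**The case against.** The strongest reply is that the regression sentence already covers this. It plans covariate adjustment, the enrolment score could be one of the covariates, and a journal article commonly leaves the covariate list to the SAP. That much stands: a reader might infer that the plan throws the enrolment scores away, but the text neither specifies nor excludes their use. What survives is that the article does choose a test for continuous outcomes, and the test it chooses is not the best one for scales measured twice.

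Second, the t-test is unbiased under randomisation. This stands too, and it limits the point to efficiency on secondary outcomes.

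Third, a reader might infer that a large share of precision is lost. The article gives no correlation. Against a 36-week t-test the saving is 9% of the variance at r = 0.3 and only 4% at r = 0.2. If the t-test is on change, the enrolment score is already in use, and at r = 0.7 the saving is 15%, not 49%.

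Fourth, the remedy has a weak spot. The first questionnaire is returned by post (Recruitment strategies), allocation follows receipt of the consent and enrolment form rather than the questionnaire (Randomisation procedure), and women are not blinded (Blinding). Some enrolment scores may be missing or completed after allocation. This is a real but small drawback, and the fix has to deal with it.

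**Conclusion.** The point holds as a recommendation of a better main analysis for four secondary outcomes: anxiety, depression, eating self-efficacy and exercise self-efficacy. ANCOVA on the enrolment score is never less precise than either form of the t-test. The saving in variance is 9% to 49% against the 36-week score and 15% to 35% against change, for r between 0.3 and 0.7. These sizes rest on an assumed r, on equal SDs at the two times for the change score, and on enrolment scores unaffected by allocation.

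Four further readings are tempting, and the article does not support them.

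- **That GDM also needs an adjusted main analysis.** The chi-squared test is valid and fits the two-proportion calculation that reproduces 185 per arm. Nothing in the article allows a gain from adjusting for BMI to be calculated.
- **That the questionnaires have the highest non-response.** One attrition rate of 15% is given, with no breakdown by outcome.
- **That covariates will be picked by observed imbalance.** The baseline check is described only as an indication of comparability and is not linked to the choice of covariates.
- **That every scale needs ANCOVA.** Readiness to change is for descriptive use and can stay so.

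**What to change.** In the Analyses section or the SAP, for anxiety, depression and each of the two self-efficacy scales:

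1. Make the main analysis an ANCOVA of the 36-week score on arm and the scale's own enrolment score. Report the adjusted mean difference with its 95% confidence interval.
2. Keep the t-test as a supporting analysis, and say whether it uses the 36-week score or the change.
3. Keep women with a missing enrolment score in the model, for example by imputing the mean enrolment score, taken over both arms together.
4. Check sensitivity to enrolment questionnaires dated after allocation, for example by treating those scores as missing.

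Leave the chi-squared test for GDM and the descriptive use of readiness to change as they are.

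The cost is a few sentences of text. No new visit, measure or participant is needed. Step 4 needs the completion or receipt date of the first questionnaire set against the allocation date. The article does not say that this date is kept, so it should be recorded if it is not.

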## Discussion

GDM is a condition that can impact on the short-term and long term health of both the mother and her baby. The risk factor of obesity is a significant contributor for this condition and the prevalence of obesity, particularly in low SES environments, is increasing. To date there is a lack of evidence to inform practice and policy to reduce the incidence of GDM and gestational weight gain so that birth outcomes are optimised. The findings of this study will inform an area of practice that is of international significance; trialling an intervention that has the potential to be sustainable in the primary care setting and may have broad application.
